## 1 INTRODUCTION

### 1.1 Background Information

Human immunodeficiency virus (HIV) infects the cluster of differentiation 4 (CD4) subset of T-cells that are critical for initiating immune responses to infection. The level of CD4 cells in the blood is a marker of a subject's immunological status. During the course of an HIV infection, the number of CD4 cells decreases, resulting in reduced immunological responsiveness and ultimately immune deficiency. Before the advent of HIV medication, it was clear that sustained immune responses to the HIV capsid protein p24 were inversely correlated with disease progression (CD4 cell decline) ([Forster, 1987](#); [Weber, 1987](#)). When CD4 counts are below  $200 \times 10^6/L$ , immune status is reduced to a level that allows for opportunistic infections. In contrast, long term non-progressor subjects show sustained immune responses to HIV p24 ([Dyer, 2008](#)). Sustained immune responses to p24 appear to be essential to maintain CD4 counts and thereby restrict disease progression.

Current management of an HIV infection includes antiretroviral therapy (ART). The advent of effective ART in 1996 led to a profound decrease in type 1 HIV (HIV-1)-associated morbidity and mortality in developed countries where ART has been available.

Despite the ability of ART to inhibit HIV-1 replication, it cannot cure infection, making ART a life-long treatment that requires sustained compliance and imposes significant individual and societal financial burdens on healthcare services. Furthermore, ART side effects (e.g., metabolic toxicity and stigmatizing body fat redistribution) often require medication that further increases the inconveniences and financial burdens of HIV management. Of additional concern is the emergence of viruses resistant to ART that can result in treatment failure.

Vacc-4x is a peptide-based HIV therapeutic vaccine. The primary objective of Vacc-4x therapeutic vaccine is to strengthen the immune system's response to HIV p24.

ART dramatically reduces the level of virus in circulation in the body, thereby allowing the immune system to focus on the therapeutic vaccine that is administered. ART also allows for the generation of new naïve CD4 cells that can be triggered by the therapeutic vaccine to generate new immune responses to HIV-1. Subjects are therefore immunized with Vacc-4x in the presence of ART to generate new HIV-specific immune responses that can sustain immunological fitness for prolonged periods when subjects are removed from ART. It is likely that periodic boosting on ART will be required to sustain the immunotherapeutic effect – in this way ART may become an intermittent therapy.

Vacc-4x is comprised of peptides that are modified from conserved domains of HIV p24, the major capsid protein of HIV. It is administered intradermally following the administration of recombinant human-granulocyte macrophage colony stimulating factor (rhu-GM-CSF), which is used as a local adjuvant. GM-CSF is specifically chosen because of its ability to facilitate dendritic cell maturation and migration to the lymph nodes for antigen presentation ([Disis, 1996](#); [Banchereau, 1998](#)). Dendritic cells are targeted because they are the most potent antigen presenting cells of the

immune system and have the capacity to carry out 'cross presentation' during which foreign antigens are presented on both human leukocyte antigen (HLA) classes 1 and 2 (Figure 1).

**Figure 1**      **Simplified Diagram Showing the Two Pathways for Peptide Digestion Leading to Presentation at the Cell Surface**

[figure not shown]

Dendritic cells ingest peptides into small vesicles. If they follow the human leukocyte antigen (HLA) class II pathway, they are cleaved within the vesicle that subsequently fuses with one carrying the HLA class II molecule. Some of the peptide fragments bind to the HLA class II and reach the cell surface attached to this molecule. The peptide fragment is recognized by a CD4 cell that docks onto the HLA molecule. Dendritic cells have the unique ability to transfer peptides to the HLA class I pathway. Here, the peptides are digested by the proteasome. The peptide fragments are then transported into specialized compartments of the cell where the HLA class I molecules reside. The peptides attach themselves to the HLA class I molecule and are transported to the cell surface. Peptide fragments are recognized by a CD8 cell that docks onto the HLA class I molecule. (From: [Sommerfelt, 2004](#))

A consequence of dendritic cell stimulation by peptides is the proliferation of both CD4 and CD8 cells. The CD8 cells acquire the ability to recognize infected cells expressing HIV epitopes that are represented in the modified peptides. The Vacc-4x therapeutic vaccine therefore aims to stimulate cell-mediated immunity.

To date, four clinical studies have been conducted with Vacc-4x. A Phase I clinical study (Study CTN B-HIV-1/99) was performed at the University of Bergen, Norway enrolled 11 chronic HIV-infected subjects ([Åsjö, 2002](#)). A Phase II clinical study (CTN B-HIV-2/2001) performed at Ullevål University hospital in Oslo, Norway enrolled 40 chronic HIV-infected subjects. Immunization started late 2002 and the study ended in 2004 ([Kran, 2004](#)). On completion of the Phase II trial, subjects that responded well to Vacc-4x had significantly reduced viral loads and correspondingly improved CD4 counts compared to low responders at the end of a three month ART-free period ([Kran, 2005](#)). Furthermore, the majority of subjects remained off ART on completion of the study, and the duration of treatment interruption was linked to immune responsiveness to the peptides ([Kran, 2006](#)). The median treatment interruption achieved for subjects was 31 months. A re-boosting study of 22 available subjects from the Ullevål study was performed in 2010 (CTN-BI/Vacc-4x/2009/1). Long-term proliferative CD4 and CD8 T cell memory was shown 7 years after

intradermal immunizations against short HIV Gag p24-like peptides targeting dendritic cells ([Lind, 2010](#); [Lind, 2012](#)). In addition, Vacc-4x has been tested in a double blind placebo-controlled multinational Phase II clinical study (CT-BI Vacc-4x 2007/1 - EudraCT Number 2007-006302-13). This study included 135 subjects. The study showed no difference in time to return to ART, or in CD4 counts over time between the Vacc-4x and the placebo group. However, The viral load set point after ART cessation varied between subjects with evidence of favorable effect of Vacc-4x immunization over placebo. There was also a significant difference in the viral load set point (mean of Weeks 48 and 52) compared to pre-ART values in the Vacc-4x, but not the placebo group. Preliminary immunological analyses shows that positive enzyme-linked immunosorbent spot assay (ELISPOT) responses to p24 in the Vacc-4x group were associated with a reduced viral load set point compared to placebo. This indicates a potential qualitative rather than a quantitative difference in immunological responses to p24 between the Vacc-4x and placebo groups. Vacc-4x was also found to be safe and well tolerated ([Rockstroh, 2011](#)).

## **1.2 Investigational Product**

Vacc-4x is comprised of peptides that are modified from conserved domains of HIV p24, the major capsid protein of HIV. Prior to the introduction of ART, it became clear that the survival time during HIV-1 infection was related to immune responsiveness to the major capsid protein p24. When immune responses to p24 declined, disease progression was accelerated. Disease progression leading to Acquired Immunodeficiency Syndrome (AIDS) is related to CD4 counts. United States (US) and European consensus guidelines from December 2007 recommend treating subjects who have CD4 counts  $\leq 350 \times 10^6/\text{L}$ . Sustained immune responses to p24 should maintain CD4 counts and delay disease progression. It has been shown that p24 antigens (not virus-associated) can persist during ART. Increasing levels of p24 antigen while on ART are inversely correlated with CD4 count and disease progression. Sustained immune responses to p24 appear to be essential to maintain CD4 counts and thereby restrict disease progression. The Vacc-4x peptides are based on conserved domains of the major capsid protein p24. Vacc-4x has induced new and sustained immune responses to p24; immune responsiveness to Vacc-4x correlated with time off ART.

### 1.3 Nonclinical Studies

#### Conclusions from Non-clinical Safety Studies – Vacc-4x

The results of single-dose toxicity studies in mice and rats ([Covance 1638/3](#); [Covance 1638/4](#)) indicate that intravenous Vacc-4x elicit no adverse reactions at doses up to 3 mg/kg. Thus, the no adverse effect level (NOAEL) was determined to be in excess of 3 mg/kg, which constitutes a 175-fold safety margin over the human dose level (1.2 mg peptides).

The safety of Vacc-4x and the adjuvant rhu-GM-CSF were also evaluated in a 22-week intradermal rabbit repeated dose toxicity study ([Covance1638/010](#)). Vacc-4x and rhu-GM-CSF were administered intermittently study weeks 1, 2, 3, 4, 12, 16, 18 and 22. The dosing regimen mimicked the regimen used in the clinical CT-BI Vacc-4x 2007/1 study up to study week 18. The administration study week 22 was in addition to the conducted clinical CT-BI Vacc-4x 2007/1 dosing regimen. Two different dose levels were evaluated, i.e. 0.12 mg/dose (1/10 of human dose) and 1.2 mg/dose (human dose). Local intradermal reactions such as erythema and edema were noted in Vacc-4x treated animals. However, similar effects were noted in control animals both macroscopically and histologically. The local reactions were slightly more pronounced in the Vacc-4x treated animals. There were no systemic adverse reactions in this study. These data indicate that Vacc-4x has no limiting toxicology in a model that is relevant to the proposed clinical study.

A 4 week intermittent intradermal administration toxicity study ([Covance 1638/011](#)) in the rabbit, with a 4-week treatment free period was done to bridge between the adjuvant Molgramostim (used in the Covance study number 1638/010, referred to as GMCSF) and the adjuvant Leukine® (sargramostim). In conclusion, the intradermal administration of Vacc-4x (1.2 mg/dose) combined with the adjuvant Leukine® or Molgramostim to the rabbit once weekly for 4 weeks was well tolerated except for local reactions. No systemic effects were noted in any parameter during the study. Local reactions at the repeat injection site were comparable for animals dosed with Leukine® or Molgramostim in addition to Vacc-4x.

### 1.4 Clinical Studies

The immunotherapy candidate, Vacc-4x, completed a Phase I clinical study at the University of Bergen, Norway, and a Phase II clinical study at Ullevål University hospital in Oslo, Norway, with a follow-up re-boosting study (EudraCT Number 2009-015249-22) and a Phase II clinical study (EudraCT Number 2007-006302-13) performed in US and Europe (United Kingdom [UK], Germany, Spain and Italy).

#### SUMMARY Phase I study ([Study CTN B-HIV-1/99](#)):

The Phase I study enrolled 11 HIV-positive subjects, including 9 subjects on ART. Subjects were maintained on ART (if entered on ART); all subjects were treated with 12 immunizations of Vacc-4x at a dose of 0.4 mg/intradermal injection over a period of 26 weeks. Immunizations were performed following injection of rhu-GM-CSF (Leucomax® [molgramostim]) as adjuvant.

*Safety Results:*

All subjects experienced one or more adverse events (AEs); nine subjects experienced events judged as related to treatment. The adverse reactions reported were mild or moderate in severity except for severe local reactions at the injection site in one subject. No subjects were withdrawn due to treatment-related AEs or toxicological reactions; no serious AEs (SAEs) occurred.

*Efficacy Results:*

All subjects experienced a cell-mediated immune response, measured by delayed-type hypersensitivity (DTH) skin reaction. Some cell-mediated immune response, measured by gamma interferon ( $\gamma$ -IFN) release using ELISPOT, was reported for 45% of the subjects; no antibody response to Vacc-4x peptides was observed.

SUMMARY Phase II Study ([Study CTN B-HIV-2/2001](#)):

The Phase II study (CTN B-HIV-2/2001) of Vacc-4x enrolled 40 HIV- positive subjects, of which 38 completed the trial. This was a dose-finding study where subjects were maintained on ART and treated with 10 immunizations at a dose of 0.4 mg (20 subjects) or 1.2 mg (20 subjects) of Vacc-4x intradermal injection, over a period of 26 weeks. Immunizations with Vacc-4x were performed following injection of rhu-GM-CSF (Leucomax [molgramostim]) as a local adjuvant. ART was interrupted from Week 26 to Week 30 to allow exposure to the subject's own virus (autologous immunization). ART was resumed from Week 30 to Week 38 to allow maturation of immune responses to the Vacc-4x peptides and to the subject's own virus. ART was discontinued from Week 38 to Week 52, when the study was formally concluded.

*Safety Results:*

No safety concern was raised during this study. No SAEs were reported during the period of immunization. One subject experienced a transient vasovagal reaction in conjunction with immunization and the DTH test at Week 26 and Week 38. A second subject experienced a vasovagal reaction in conjunction with the DTH test at Week 52. For the laboratory parameters, vital signs, and performance status, no changes attributable to immunization were observed. Changes in HIV ribonucleic acid (RNA), CD4 cell counts, and CD8 cell counts showed no safety concerns related to immunization.

*Efficacy Results:*

Immunological responses reported as DTH-positive reactions were observed for all subjects. Overall, positive responses both for induration and erythema were statistically significantly higher in the high dose (HD, 1.2 mg Vacc-4x) group compared to the low dose (LD, 0.4 mg Vacc-4x) group. The dose-dependent differences in DTH reactions were maintained throughout the study. T-cell proliferation appeared stable after Week 12 and demonstrated an HD advantage, consistent with the DTH results. ART was interrupted at Week 38 with planned re-start when CD4 counts fell to less than 200/ $\mu$ L or when AIDS- or HIV-related events were observed (i.e. clinical practice). DTH responses to Vacc-4x (high versus low response determined at Week 38) were associated with reduced viral loads and correspondingly improved CD4 counts at the end of the study (Week 52).

During the immunization period, CD4 counts were stable or increased. Interruption of ART resulted in reduction of CD4 counts. However, 14 weeks after the last interruption of ART (Week 52), the mean CD4 counts were still above  $200 \times 10^6$  cells/L. No difference between the LD and the HD groups was observed. The majority of subjects remained off ART following completion of the study (Week 52); permission was given to follow the subjects until they resumed ART. The duration of treatment interruption was linked to immune responsiveness to the peptides. When study subjects were compared to similar subjects in the Netherlands that had stopped treatment without immunotherapy, a significantly slower decline in CD4 cells was noted for the Vacc-4x subjects. The median treatment interruption achieved for all subjects that participated in the Vacc-4x Phase II clinical study was 31 months.

In a follow-up study of 26 of these subjects ([CTN-BI/Vacc-4x/2009/1](#) - EudraCT Number 2009-015249-22), seven years after immunization, most subjects who earlier had responded to Vacc-4x now showed detectable CD4 memory cells which could be activated.

SUMMARY Phase II Study (CT-BI Vacc-4x 2007/1 - EudraCT Number 2007-006302-13):

This study was performed in US and Europe (UK, Germany, Spain and Italy). The study was a randomized, double-blind, multicenter, immunogenicity study of Vacc-4x versus placebo in subjects infected with HIV-1 who had maintained an adequate response to ART. The primary objective was to evaluate the effect of Vacc-4x immunizations versus placebo on CD4 counts, T-cell function (ELISPOT, T-cell proliferative responses and intracellular cytokine staining) and the response to interruption of ART. The study was planned to include approximately 345 subjects but due to recruitment difficulties the study was amended to reduce the planned number of subjects to a minimum of 120 subjects. Due to reduced numbers of subjects the Food and Drug Administration (FDA) responded as follows: “Due to the size (N=130) and nature (no formal hypothesis testing) of this study, please understand that CBER [Center for Biologics Evaluation and Research] will regard this study as exploratory and for hypothesis-generating purpose only”. Following the FDA response it was important to look more in detail into the data by including post-hoc analyses.

It was concluded that Vacc-4x did not reduce the proportion of subjects requiring resumption of ART after ART cessation at Week 28 in comparison with placebo. In addition, there was no effect compared with placebo on the percentage change in CD4 count between Week 28 and the last CD4 assessment before resumption of ART.

The time to restarting ART was similar in Vacc-4x and placebo-treated subjects.

The viral load set point (mean of the last two viral load determinations before ART resumption or at study end at week 52) varied between subjects with evidence of favorable effects of Vacc-4x immunization over placebo. In the subgroup of “completer” subjects who remained off ART until Week 52, the median viral load set point was significantly lower ( $p = 0.0397$ ) in the Vacc-4x-treated subjects (22300 copies/ml,  $n = 56$ ) compared to placebo-treated subjects (61900 copies/ml,  $n = 25$ ). In the subgroup of “LOCF” (last observation carried forward), including all subjects off ART until at least Week 40, the median viral load set point was lower in the Vacc-4x group (26775

copies/ml, n = 72) compared to the placebo group (57975 copies/ml, n = 32), but this difference did not reach the level of statistical significance (p = 0.1489).

No safety concern was raised during this study. The study was supervised by a Data Safety Monitoring Board (DSMB).

## **1.5 Rationale for the Current Study**

This study is a follow-up, re-boosting study of Study CT-BI Vacc-4x 2007/1 (EudraCT Number 2007-006302-13) performed in US and Europe (UK, Germany, Spain and Italy). All subjects to be included have been given a therapeutic immunization with Vacc-4x during the CT-BI Vacc-4x 2007/1 study. During the study a reduction in the viral load set-point (mean viral load at Week 48 and Week 52, or if Week 52 not reached, mean viral load of the last two measured values before restart of ART) was seen in the Vacc-4x group compared to placebo group. Further stimulation of the immune system by re-boosting with Vacc-4x could reduce the viral load set-point further. The study is open because the number of subjects available is limited.

### **1.5.1 Dose**

The re-boosting dose will be 1.2 mg of Vacc-4x, the same as given in Study CT-BI Vacc-4x 2007/1 (EudraCT Number 2007-006302-13).

### **1.5.2 Re-boosting Schedule**

The subjects will receive two re-boosting immunizations with a 2 weeks interval between immunizations.

### **1.5.3 Use of Adjuvant GM-CSF**

Peptide vaccines are poorly immunogenic by themselves. To induce measurable levels of T-helper cell type 1 (Th1) or type 2 (Th2) immune responses against these peptides an adjuvant is often required. Recombinant human GM-CSF was selected for the development of Vacc-4x based on its adjuvant activity when given in combination with protein and peptide antigens ([Hodge, 2006](#); [Arellano, 2004](#)). GM-CSF facilitates dendritic cell maturation and migration to the lymph nodes for antigen presentation ([Disis, 1996](#); [Banchereau, 1998](#)) and is indicated for other uses, such as chemotherapy and transplantations. Following chemotherapy, GM-CSF is administered subcutaneously at an initial recommended dose of 3 µg/kg/day, followed by a maintenance dose between 0.3 and 8 µg/kg/day; however, when using GM-CSF as an adjuvant, GM-CSF is administered intradermally at much lower doses ([Gjertsen, 2001](#); [Brunsvig, 2006](#); [Bernhardt, 2006](#)). In the Vacc-4x program, 0.33x10^6 international units (IU) GM-CSF is used (irrespective of body weight), a dose which is considered to be safe and sufficient to induce a local response. Other studies have also demonstrated the safety and potential usefulness of GM-CSF in this setting ([Sasaki, 2003](#)). GM-CSF administered subcutaneously may induce modest, but not clinically significant, increases in plasma HIV type 1 RNA levels and CD4 lymphocyte counts in subjects with uncontrolled HIV infection ([Jacobson, 2003](#)); however, in the current study, as in preceding

ones, subjects will be exposed to commercial GM-CSF (Leukine® sargramostim, rhu-GM-CSF) while on ART when viremia is controlled.

## **1.6 Potential Risks and Benefits**

Participants will provide important scientific information that may contribute to improved future vaccination of HIV-positive subjects. Potential benefits for participants include a possible sustained improvement in the immune response to p24 and HIV. Potential risks include the discomfort and inconvenience associated with the immunizations and the risk of known or unknown side effects of exposure to Vacc-4x and Leukine® including, most commonly, local reactions at the site of injections and fatigue (incidence not yet determined). However, since all subjects in this study have participated in Study CT-BI Vacc-4x 2007/1 (EudraCT Number 2007-006302-13) they are aware of potential discomfort.

Interruption of ART for extended periods is associated with an increased morbidity and mortality, thus planned long-term therapy interruption strategies are not recommended outside of controlled clinical trials (Department of Health and Human Services [DHHS] Guidelines for the Use of Antiretroviral Agents in HIV-infected Adults and Adolescents, January 29, 2008). In the present study the subjects are stopping ART for a relatively short period of up to 16 weeks, during which they will be closely monitored.

The subjects will remain on ART throughout the immunization period and for another 10 weeks after the final immunization, in order to prevent interference from the immune response caused by viral rebound associated with ART interruption. In all studies with Vacc-4x, subjects have been vaccinated when on ART with no loss of viral control. Viral rebound was only observed after subjects stopped ART. During the ART interruption period, subjects are being monitored carefully and ART will be restarted if subjects exceed pre-specified criteria for viral load and CD4 reduction or for any other medical reasons (4.4.1.3 Criteria for Restart of ART).

## **2 STUDY OBJECTIVES AND ENDPOINTS**

### **2.1 Study Objectives**

#### **2.1.1 Primary Objective**

The primary objective of this study is to evaluate if a re-boost with Vacc-4x could

a) reduce the viral load set-point, and

b) increase the immune response obtained following immunization with Vacc-4x in Study CT-BI Vacc-4x 2007/1 (EudraCT Number 2007-006302-13).

#### **2.1.2 Secondary Objectives**

- To evaluate the effect of a re-boost with Vacc-4x on CD4 counts and CD8 counts.

- To assesses *in vivo* immunogenicity of Vacc-4x by evaluation of DTH and to compare the DTH response to the DTH response observed in the initial study; CT-BI Vacc-4x 2007/1 (EudraCT Number 2007-006302-13).
- To evaluate the safety and tolerability of re-boosting with Vacc-4x.

## **2.2 Study Endpoints**

### **2.2.1 Efficacy Endpoints**

#### **2.2.1.1 Primary Efficacy Endpoints**

- Viral load set point (mean of VL count Visit 8 and Visit 9) for subjects discontinuing ART according to protocol and *not* resuming ART until Visit 9 compared to:
  - viral load set point\* for subjects not resuming ART before week 52 or later in the CT-BI Vacc-4x 2007/1 study and who entered this study,or if week 52 not reached in the previous study
  - viral load set point\*\* for subjects resuming ART at the earliest week 40 in the CT-BI Vacc-4x 2007/1 study and who entered this study.

*\* The VL set point was defined as the mean of VL count week 48 and week 52 week in subjects who did not resume ART.*

*\*\*The VL set point was defined as the week 40 VL count for subject resuming ART week 40 or the mean of the last two VL counts prior to ART resumption for subjects resuming ART week 44 or later but before week 52.*

Comparison will also be made to pre-ART viral load values, if available from the CT-BI Vacc-4x 2007/1 study.

- T-cell response will be measured by ELISPOT as well as by T-cell proliferative response assay (Flow Cytometry) and intracellular cytokine staining at Visit 2 (before re-boosting), Visit 4 (two weeks after re-boosting), Visit 6, Visit 9 and Visit 10. These will be compared to the responses reported in the study CT-BI Vacc-4x 2007/1.

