### **4.2 Inclusion Criteria**

1. Completed immunization regimen with Vacc-4x active and stopped ART (at Week 28) in the CT-BI Vacc-4x 2007/1 study. (No re-start of ART is required).
2. Documented pre-study CD4 cell count  $\geq 400 \times 10^6/L$ .
3. Documented pre-study viral load  $< 300\,000$  copies/mL.
4. Signed informed consent.

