### **6.3.2.4 Visit 5**

This visit should be 84 ( $\pm 3$ ) days from Visit 2.

If on ART, the subject will be instructed to now stop ART if their CD4 count is  $\geq 350 \times 10^6/\text{L}$  and virally controlled (undetectable VL [ $<50$ copies] over a period of three months on a stable antiretroviral regimen with no more than one blip allowed). If the CD4 count is  $<350 \times 10^6/\text{L}$  and/or the virus is not controlled, the subject will be instructed to remain on ART. The instruction will be based on the results of CD4 count and viral load from this visit. As soon as possible when these

results are available, and at the latest within one week after this visit, the investigator will contact the subject by phone and tell the subject to stop ART, or not to stop ART. Stopping of ART will be done according to local guidelines and their current clinical judgment and based on the individual ART the subjects are receiving. Subjects will be instructed to write down the date(s) when stopping ART and take this information to the investigator at the next visit.

The Investigator needs to see the results from the blood sampling at Visit 5 before the subject can stop ART. The information to the subject that he/she can stop ART and instructions on how to do this can be made by telephone. It is important that the treatment interruption period has a full 16 week duration.

The following procedures will be performed:

- Review of concomitant medications and AEs.
- Physical examination including weight.
- Vital signs (blood pressure, heart rate).
- Clinical chemistry and hematology.
- Viral load, CD4 and CD8 counts.

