#### **6.3.3.3 Visit 8**

This visit should be 168 ( $\pm 7$ ) days from Visit 2.

The following procedures will be performed:

- Review of concomitant medications and AEs.
- Vital signs (blood pressure, heart rate).
- Clinical chemistry and hematology.
- Viral load, CD4 and CD8 counts.

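### The primary viral load comparison sets 12 and 16 weeks off ART against 20 and 24 weeks for initial-study completers, and against about 12 to 20 weeks for earlier resumers, so time off ART cannot be separated from a re-boost effect

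*Protocol*

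**What the plan says.** Protocol section 2.2.1.1 defines the re-boost value as "Viral load set point (mean of VL count Visit 8 and Visit 9"), for subjects who stop ART as planned and do not resume before Visit 9. The comparator comes from the same subjects in the initial study and has two forms:

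- Not resuming before week 52: "mean of VL count week 48 and week 52 week in subjects who did not resume ART".
- Resuming from week 40 to before week 52: the week 40 value for a subject resuming at week 40, otherwise the mean of the last two values before resumption.

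Section 4.2 admits only subjects who "stopped ART (at Week 28) in the CT-BI Vacc-4x 2007/1 study". In the present study ART is stopped at Visit 5 (nominal day 84), and Visits 8 and 9 are at nominal days 168 and 196 (Table 1). Section 10.6.2.1 makes the paired Wilcoxon signed rank test of these values the primary comparison. The study is open and non-randomized, with no reference product.

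On the interruption itself, section 6.3.2.4 says "It is important that the treatment interruption period has a full 16 week duration". It also has the stop instruction given by telephone once the Visit 5 results are known, "at the latest within one week after this visit", while all visits are counted from Visit 2.

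**The concern.** A within-subject comparison of two interruptions is informative about the re-boost only if the two readings are taken at comparable points in each interruption. Here the definition fixed in the protocol places them at different points for one type of subject and at roughly similar points for another. Which type a subject belongs to depends on how the first interruption went. Nothing in sections 2.2.1.1 or 10.6.2.1 matches or adjusts for time off ART.

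If viral load is not flat between about 12–16 and 20–24 weeks off ART, the change over that interval enters the paired difference as though it were due to the re-boost. Without a concurrent control there is nothing to subtract it. The result could favor the re-boost or hide a real effect.

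**Working it through.** **Inputs.** ART stop in this study: day 84 (section 6.3.2.4). Visits 8 and 9: days 168 and 196 (sections 6.3.3.3 and 6.3.3.4). ART stop in the initial study: week 28 (sections 4.1 and 4.2). Comparator weeks: section 2.2.1.1. Initial-study Vacc-4x counts: 72 off ART to at least week 40, of whom 56 to week 52 (section 1.4).

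**Step 1: reproduce the stated period.** (196 − 84)/7 = 16 weeks, which agrees with the 16-week ART-free period in section 10.6.2.1.

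**Step 2: time off ART at each reading.** Re-boost: (168 − 84)/7 = 12 and (196 − 84)/7 = 16 weeks, mean 14. The gap below is the comparator mean minus 14.

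| Initial-study subject | Weeks used | Weeks off ART (week − 28) | Mean | Gap |
|---|---|---|---|---|
| Off ART to week 52 | 48, 52 | 20, 24 | 22 | +8 |
| Last two values at weeks 44, 48 | 44, 48 | 16, 20 | 18 | +4 |
| Last two values at weeks 40, 44 | 40, 44 | 12, 16 | 14 | 0 |
| Resumed at week 40 | 40 | 12 | 12 | −2 |

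If the week 44 sample is not counted as prior to resumption, a week 44 resumer contributes weeks 36 and 40, that is 8 and 12 weeks off ART (mean 10, gap −4).

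**Step 3: can visit windows close the gap for completers?** The most generous reading puts Visit 9 at 196 + 7 − (84 − 3) = 122 days, or 17.4 weeks, after the stop. That is still short of 20 weeks.

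**Step 4: how many subjects might be affected?** In the initial Vacc-4x group, 56/72 = 78% fall under the weeks 48/52 rule and (72 − 56)/72 = 16/72 = 22% under the fallback rule. The split among re-boosted subjects is not given.

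**Step 5: illustration of size.** The protocol gives neither a drift nor an SD, so both are assumed. Drift here means the mean change in log10 viral load between the two periods off ART. The signed rank test was simulated at two-sided 5% with no re-boost effect, normal paired differences, SD 0.4–0.6 log10 and n=20–40. Section 10.1 expects 30–40 eligible; the lower n allows for subjects who do not stop ART or who restart before Visit 9.

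| Drift (log10) | All subjects with full gap | 22% with no gap |
|---|---|---|
| 0 | about 5% | about 5% |
| 0.1 | about 10–32% | about 8–22% |
| 0.2 | about 28–86% | about 18–63% |

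The low end of each range is n=20 with SD 0.6; the high end is n=40 with SD 0.4. Repeat runs move the figures by about one percentage point.

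**Step 6: the schedule passages.** With nominal visit days and the instruction given a full week after Visit 5, Visit 9 falls 196 − 84 − 7 = 105 days (15 weeks) after the stop, against 16 × 7 = 112 days for a full 16 weeks.

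**The case against.** The strongest reply is that a set-point is meant to be a plateau, so the exact week should not matter. The initial study's own rule accepts a single value at 12 weeks off ART as a set-point. That is a fair reading of the sponsor's premise, but the protocol shows no viral load course to support it. The opposite is equally unproven. What stands is that drift is a possibility, not an established fact.

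A second reply is that the aim (section 3.2) is to lower the set-point achieved after the first regimen, which section 1.5 describes at weeks 48 and 52 for completers, so a weeks 40/44 comparator asks a somewhat different question. This stands, and is a reason to keep the weeks 48/52 comparison. It does not make that comparison interpretable by itself.

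A third is that section 10.5.2 leaves subgroups by ART timing to the SAP. Those subgroups concern timing in the present study only and do not alter the comparator fixed in section 2.2.1.1.

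Three stronger readings are tempting and are not supported:

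- *That every subject carries the 8-week gap.* The fallback rule puts earlier resumers close to matched times.
- *That the rejection rates are the risk of a false claim of benefit.* They are two-sided. Only rejections in the favorable direction would be false claims of benefit. If the drift ran against the re-boost, those would fall below the nominal 2.5% (under 0.5% in simulation at 0.1 log10 with every subject affected).
- *That Visit 9 falls within firm limits of 95 to 122 days after the stop.* The upper figure needs ART to stop on the day of Visit 5, yet the investigator must first see that visit's results. The lower figure, 196 − 7 − (84 + 3 + 7) = 95, treats the limit on the telephone call as a limit on the stop date.

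**Conclusion.** The concern holds in this form. For initial-study completers the primary comparison sets 12 and 16 weeks off ART against 20 and 24. For earlier resumers the comparator is at about 12 to 20 weeks (8 and 12 under the narrow reading of prior). The pooled paired differences thus mix gaps of about 0 to 8 weeks. This follows from the protocol's own dates and needs no assumption.

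How much harm results does rest on assumptions. Under those in the illustration, even a 0.1 log10 drift lifts two-sided rejection from 5% to somewhere between about 8% and 32%, depending on n, SD and the share of subjects with no gap. The protocol supports neither a size nor a direction for the drift, so it cannot be said that the design favors the vaccine. It can be said that a difference in either direction could not be attributed to the re-boost on this comparison alone.

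The mismatch between visit counting, the delayed stop instruction and the full 16-week statement is a separate and lesser point.

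**What to change.** In sections 2.2.1.1 and 10.6.2.1, pre-specify a time-matched paired comparison: the mean of Visits 8 and 9 against the mean of initial-study weeks 40 and 44 (28 + 12 and 28 + 16), or Visit 8 against week 40 where only week 40 exists. First confirm that weeks 40 and 44 values are available for completers; the fallback rule implies such sampling but does not state it for them. Use the ART stop date, already recorded at Visit 6 (section 6.3.3.1), to check the match in actual days.

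Preferably make this the primary comparison and keep the weeks 48/52 set-point as secondary. At the least, report it beside the set-point comparison, and do not attribute a difference to the re-boost unless the matched comparison agrees.

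The cost is endpoint wording; no visit or sample is added. The downside is that the comparator is no longer the previously reported set-point. Matching removes the nominal 8-week gap but does not supply a control: two successive interruptions may still differ for other reasons.

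Separately, reconcile the passages that count visits from Visit 2, allow the stop instruction up to one week after Visit 5, and call for a full 16-week interruption.
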